### Recruitment {15}

The Mgambo JKT camp enrols 2000 recruits in every annual intake. We aim to recruit at least 1500 to the study. If new recruits join an existing combania in the trial, they will be approached for enrolment.

### Assignment of interventions: allocation

#### Sequence generation {16a}

Randomisation of the combania will be carried out by an independent statistician using a random number generator in R or Stata.

#### Concealment mechanism {16b}

Manufacturers of the uniforms and repellents will prepare active and placebo uniforms and repellent and placebo lotions in identical containers identifiable by a 6-digit code sewn into the uniform or applied on the lotion bottle. Each combania will be allocated an identification code. There will be one code per combania, to limit the effect of accidental unblinding, and a separate code for additional untreated uniforms and placebo DEET, in case of adverse events.

#### Implementation {16c}

The combania will be allocated to the intervention by an independent statistician, who will carry out the randomisation and retain the codes. This statistician will not be further involved in the trial. The code master list will be provided to a site manager by the statistician using email to ensure concealment. Uniforms and lotion will be assigned to combania by the study site manager following the code master list.

### Assignment of interventions: blinding

#### Who will be blinded {17a}

In this double-blinded placebo-controlled trial, the participants, investigators and study statistician will be blinded to the allocation of interventions by a combination of intervention codes and combania codes.

#### Procedure for unblinding if needed {17b}

In the advent of a severe adverse event thought to be connected to the intervention, the recruit will be allocated untreated uniforms. The time contributed to the study by a person who experienced an adverse event will be included in the intention-to-treat analysis. Unblinding of the participant will be carried out if necessary to allow the study doctor to provide appropriate care. Only the study doctor will be informed of the person’s intervention allocation; other participants and investigators will remain blinded. The IHI Institutional Review Board will be informed of the adverse event.

### Data collection and management

#### Plans for assessment and collection of outcomes {18a}

Data collection will be via questionnaires “Additional file 1” loaded onto tablet computers and uploaded every 2 weeks via mobile phone network to the IHI server, where the data will be checked and verified monthly by the study investigators.

Participants who are symptomatic (fever, defined as axillary temperature ≥ 38 °C; chills; headache; nausea and vomiting; muscle pain; fatigue) will be tested for *Plasmodium* infections using malaria rapid diagnostic tests (mRDTs) at point of care for clinical diagnosis. RDT data will also be uploaded in real time from tablet computers. During active case detection, every 2 weeks, a blood spot will be taken on Whatman filter papers [41] for analysis by real-time PCR [42] at Ifakara Health Institute. Each sample (RDT, filter paper and blood slides) will be labelled with participant identification number, combania and date. Treatment will be offered to all malaria-infected participants, and all treatment details will be filled in and added to the patient file.

Data from PCR analysis of blood spots taken to capture subpatent malaria cases will be entered into tablet computers at the laboratory for inclusion in the study data set. Data will be checked for quality before incorporation into the central database.

#### Plans to promote participant retention and complete follow-up {18b}

Participants in this trial are military recruits who are expected to stay in the camp for at least 2 years. The trial is designed to conclude before the end of voluntary participation in national service. However, new recruits joining an existing combania will be asked if they wish to enrol and recruits who leave the camp will not be followed up. The time when the recruits are on leave will not be included in the period of follow-up.

#### Data management {19}

Data will be collected using tablet computers and uploaded weekly to the IHI server. Access to the data will be password controlled. Data cleaning will be conducted weekly and will incorporate checking for outliers, unusual values, inconsistencies and missing entries. This will be followed by fixing structural errors, removing duplicates, correcting unusual values for which a true value can be located, and removing unusual values for which a true value cannot be located [43].

To minimise data entry errors, questionnaires and data sheets on tablet computers will be programmed to give warnings when values outside of the expected range are entered, when the type of value entered is incorrect (for example, a numeric value rather than text), when a mandatory field is omitted and when identical values are entered.

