##### DEET

Each participant from a combania that receives DEET will be given a 120-mL container of 30% DEET repellent (Lipo DEET) for topical application, and the container will be replaced every 2 weeks. Combania in placebo arms will be given 120 mL of placebo lotion. The DEET lotion and its placebo will be prepared by Sawyer Ultra 30. Participants will be instructed to apply the repellent topically twice daily: once in the morning and once in the evening. One application of Lipo DEET protects for up to 12 h and has a pleasant odour and non-greasy feel on the skin. This liposome-based repellent is the newest advance in insect repellent technology. Like the earlier generation of polymer-based controlled release systems, the liposome envelops the active ingredient, DEET, and slowly releases it as needed, thereby extending the repellent’s effectiveness. DEET was selected for this study because it has been extensively tested for safety and toxicity for human use [28–30] and for its efficacy against a broad variety of arthropod vectors [31–33]. DEET was first registered in 1957 and has an excellent safety profile [34, 35].

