#### Defining compliance

Compliance with the intervention will be estimated as the proportion of 2-week time intervals where the participant was compliant and estimated by study arm and over time. The JKT recruits must wear uniforms and will be provided with two treated uniforms. They have no alternative clothing, leading to an expected 100% compliance; compliance with clothing will not be monitored. Participants’ repellent bottles will be weighed twice weekly to estimate application rates. If a bottle contains more than 50% of the required dose, the participant will be recorded as non-compliant.

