#### Methods in analysis to handle protocol non-adherence and any statistical methods to handle missing data {20c}

We expect that there will be little missing data since there will be active follow-up during the trial. For all analyses, participants will be included for all time points where their data is not missing. If there is missing data, we will conduct sensitivity analyses to check that the calculations are not affected.

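### The cleaning rule removes unusual values that cannot be traced, so it can delete genuine extremes, including the bottle weights that define compliance; the direction and size of any bias are not established

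*Protocol article*

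**What the plan says.** In the Protocol article, Data management {19} describes the cleaning: "Data cleaning will be conducted weekly and will incorporate checking for outliers, unusual values, inconsistencies and missing entries". Two steps then deal with unusual values. The first is "correcting unusual values for which a true value can be located", and the second, for the rest, is "removing unusual values for which a true value cannot be located". The same section has the tablets "programmed to give warnings when values outside of the expected range are entered", and also "when a mandatory field is omitted and when identical values are entered"; these entry checks warn and do not delete.

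Compliance with the lotion rests on bottle weights. Under Defining compliance, "If a bottle contains more than 50% of the required dose, the participant will be recorded as non-compliant", and compliance is the proportion of 2-week intervals in which the participant was compliant. The DEET subsection gives each participant a 120-mL bottle and says "the container will be replaced every 2 weeks". Estimating compliance is listed under Secondary objectives. The per-protocol analysis in section {20a} excludes 2 weeks of follow-up for participants who did not comply with the lotion.

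On missing data, section {20c} says "For all analyses, participants will be included for all time points where their data is not missing", and promises sensitivity analyses if any data are missing.

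**The concern.** Being unusual is not evidence of error. A rule that deletes whatever looks odd and cannot be traced will also delete true values that happen to be extreme. A value is extreme because of what it measures, so losing it may be informative.

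Bottle weights are where this matters most. They are a continuous measurement, a single reading can settle whether a fortnight counts as compliant, and both ends of the range are physically possible: a bottle that was hardly touched and one that was emptied. If such weights were removed, the compliance estimates by arm and over time could shift, and the per-protocol classification with them. If DEET and placebo lotion were used differently, the number of deletions could also differ between arms, even with everyone blinded. Values deleted during weekly cleaning may be hard to restore later.

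**Working it through.** The plan gives no figure for the effect of cleaning, so there is none to reproduce. The check has two parts.

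**1. What the text fixes and what it leaves open**

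- *Trigger for removal:* unusual and untraceable. Impossibility or demonstrated error is not required (Data management {19}).
- *Definition of unusual:* none in that section.
- *Exemptions:* none, so bottle weights fall under the rule.
- *Status of a nearly full bottle:* Defining compliance gives it a regular category, non-compliant. No section calls it unusual.
- *Scope for rechecking a weight:* under Strategies to improve adherence {11c}, used containers are weighed at the 2-weekly replacement, so staff hold the container when they enter the weight. Defining compliance instead has bottles weighed twice weekly, which would give neighbouring readings. Neither section says that containers are kept afterwards.

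The rule can therefore reach genuine weights. Whether it would, and which ones, the text does not say.

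**2. What deletion would do to reported compliance**

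Inputs:

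- c = true compliance = 0.80, the planning value in Sample size {14}
- f = share of non-compliant records deleted (assumed; not in the documents)
- g = share of compliant records deleted (assumed; not in the documents)

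Reported compliance = c(1 − g) / [c(1 − g) + (1 − c)(1 − f)]

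| f | g | Calculation | Reported compliance |
|---|---|---|---|
| 5% | 0 | 0.80 / (0.80 + 0.20 × 0.95) = 0.80 / 0.99 | 80.8% |
| 10% | 0 | 0.80 / (0.80 + 0.20 × 0.90) = 0.80 / 0.98 | 81.6% |
| 25% | 0 | 0.80 / (0.80 + 0.20 × 0.75) = 0.80 / 0.95 | 84.2% |
| 50% | 0 | 0.80 / (0.80 + 0.20 × 0.50) = 0.80 / 0.90 | 88.9% |
| 10% | 10% | 0.72 / (0.72 + 0.18) = 0.72 / 0.90 | 80.0% |
| 0 | 10% | 0.72 / (0.72 + 0.20) = 0.72 / 0.92 | 78.3% |

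As a share of all bottle-fortnights, the deletions in the rows with f = 10%, 25% and 50% and g = 0 are 0.20 × f = 2%, 5% and 10%. The 88.9% row thus requires half of all non-compliant fortnights to be lost and no compliant ones.

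The sign depends only on whether f is above or below g. Compliance is overstated if f > g, unchanged if f = g and understated if f < g.

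**Per-protocol analysis.** If section {20c} drops the fortnight whose weight was deleted, a non-compliant fortnight leaves the analysis just as it would under {20a}, and only compliant person-time is lost in error. If the fortnight is kept because nothing marks it as non-compliant, the per-protocol set is contaminated. These outcomes exclude each other, and the article does not say which applies to a missing weight.

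**The case against.** A reader might infer more: that an untouched bottle is the obvious outlier, that its weight can rarely be verified after the exchange, and that the rule therefore strips out non-compliance and inflates the compliance estimate. There is some reasoning behind this. If the required dose is close to the bottle's contents (an assumption, since the volume per application is not given) and 80% of fortnights are compliant, most final weights would lie in the lower half of the range, and a full bottle would be the possible value furthest from the bulk. A spilled bottle may simply look used, and a lost one is missing rather than unusual, so neither clearly offsets the effect.

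The documents still do not support that reading. They give a nearly full bottle a valid category, planning expects about 20% non-compliance, and the background section says that daily repellent use rarely reaches what is needed. Such bottles are expected findings. The container is in hand at weighing, warnings appear at entry, and a fortnightly adherence questionnaire gives a second source. Suspiciously light bottles could be removed as well, which pushes the other way. Nothing in the text establishes f > g.

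The clause can also be read as ordinary error correction: a value with a separate true value is a suspected mistake, whereas a genuine full-bottle weight is itself the true value. That is probably the intent, but the wording does not limit removal to errors.

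Two further defences carry less weight. The promised sensitivity analyses are unspecified, and analyses confined to the remaining data cannot show what was removed for being extreme. Detailed query rules do usually belong in a data management plan or SAP, and their absence here is no fault; the point rests on a removal rule that the article does state.

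**Conclusion.** The point holds as a minor one. The stated rule permits deletion of genuine but extreme values, bottle weights among them, and these feed a secondary objective and the per-protocol exclusions. Neither selective removal of unused bottles nor an overstatement of compliance is shown.

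The illustrative range at 80% true compliance runs from 78.3% (only compliant records lost, 10% of them) through 80.0% (equal loss) to 81.6% (only non-compliant records lost, 10% of them). It reaches 88.9% only in the extreme case of half the non-compliant records lost and no others. All of these deletion rates are assumptions.

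The primary intention-to-treat incidence rate ratio is built on infections and time at risk, not on bottle weights, and is essentially unaffected.

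**What to change.** Replace the removal clause in Data management {19} with a rule along these lines: only physically impossible values are set to missing (for a bottle, a weight above that of a full container or below that of an empty one); values that are unusual but possible are queried, flagged and kept. Report the number of values set to missing by arm, and show compliance with all recorded values included as a sensitivity analysis.

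The cost is one sentence in the protocol and one extra table in the report, with no new data. The Trial status section says that recruitment has not begun, so the change can be in place before any weight is recorded.

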#### Confidentiality {27}

To maintain participants’ confidentiality, data will be pseudonymised before analysis. Participants will be identified not by name but by codes known only to the researchers. The trial will report aggregate findings at combania and study arm levels but not individual findings.

#### Plans for collection, laboratory evaluation and storage of biological specimens for genetic or molecular analysis in this trial/future use {33}

Not applicable; blood samples will be used only for malaria diagnosis.

### Statistical methods

#### Statistical methods for primary and secondary outcomes {20a}

The primary analysis will be an intention-to-treat analysis. A per-protocol analysis will also be performed where person-time at risk will be adjusted to exclude 2 weeks of follow-up of participants who (1) have not complied with the lotion, (2) have taken antimalarials or (3) have travelled outside the camp for personal reasons within the previous 2 weeks. Statistical analysis will be done in Stata (StataCorp, College Station, TX, USA) and R (The R Foundation for Statistical Computing, Vienna, Austria).

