### Relevant concomitant care permitted or prohibited during the trial {11d}

Participants are advised to refrain from self-prescription of any medication. All antimalarials will be dispensed to only participants with positive RDT.

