### Outcomes {12}

#### Primary outcome

The primary outcome is the incidence of *Plasmodium falciparum* infection as determined by active case detection through quantitative polymerase chain reaction (qPCR) in blood samples taken every 2 weeks and by passive case detection at the camp clinic in the case of illness. Personal travel by participants will be assessed every 2 weeks with brief questionnaires to estimate time away from the camp. Time at risk will exclude a 14-day period post-travel and a 14-day prophylactic period following any malaria treatment. Malaria infections will be detected by qPCR; this method detects malaria infections below the limit of detection (LOD) of rapid diagnostic tests (RDTs), although RDT will be used at the point of care for any participants symptomatic for malaria. We will perform the PlasQ qPCR assay as described previously [36]. This triplex TaqMan chemistry-based qPCR assay detects the pan-*Plasmodium* 18S rRNA sequence (PSpp18S) [37, 38] and the *P. falciparum*–specific acidic terminal sequence of the var genes (PfvarATS) [39]. The human RNaseP (HsRNaseP) gene serves as an internal control to evaluate the quality of DNA extraction and qPCR amplification. After finger-pricking by a study nurse, a blood sample of 200 μL of whole blood is drawn into an EDTA-containing collection tube (Greiner, MiniCollect®); 180 μL of the whole blood will be mixed with an equal volume of DNA/RNA Shield™ (Zymo Research, Irvine, CA, USA) and incubated at room temperature for 30 min before storage at –20 °C. On a weekly basis, samples will be packed with liquid nitrogen in a thermo-col container and transported under cold chain to the qPCR facility. A temperature long will be used on the storage at the field facility, during transport and at the qPCR facility. Upon arrival, DNA will be extracted from the samples using Quick-DNA™ MiniPrep kits (Zymo Research, Irvine, CA, USA), following the manufacturer’s guidelines. Amplification and qPCR measurements will be performed using the Bio-Rad CFX96 Real-Time PCR System (Bio-Rad Laboratories, Hercules, CA, USA). All qPCR runs will be performed with a no-template control (NTC) and with *P. falciparum* NF54 DNA as a positive control.

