## Discussion

Better ways to protect military personnel from malaria on active duty are required. Findings from the proposed trial will provide knowledge to improve malaria prevention among military personnel. We will provide information on which combination of interventions is most effective and may reduce unnecessary costs to institutions, such as the cost of topical repellents. Identifying factors for non-adherence may improve the design of future bite prevention interventions.

The trial will evaluate the impact of interventions in an active duty environment. The results may be relevant to other occupations with exposure to an increased risk of mosquito bites and vector-borne disease, including forest workers, guards and miners, loggers and rubber tappers [45]. If beneficial, other potential users could include visitors to endemic regions [46], relief workers [47] and refugees [48].

Insecticide-treated clothing may also protect wearers from day-biting mosquitoes, such as *Aedes aegypti*, which are currently increasing rapidly in Tanzania [49], as well as other arthropods that engage in nuisance biting. This trial will not test efficacy against dengue but may generate data needed for Tanzanian registration of insecticide-treated clothing that could have benefits for multiple vector-borne diseases. Etofenprox has not previously been put into a trial that estimates efficacy in combination with another repellent. Due to low toxicity and environmental safety [50], vendors may find a new niche in the community for impregnating clothes with the repellent.

The study involves a group of young people who, because they must wear their uniform as part of their job, will be more likely to comply effectively with the intervention than would the general population. While this is necessary to determine the true effect of insecticide-treated clothing to reduce disease under controlled conditions, the results may overestimate the effectiveness of the intervention for the general population. However, it is likely that compliance among military personnel will be similar to that among other users whose occupations require them to wear uniforms, such as guards, miners and nurses. This may influence generalizability of the findings, as the effectiveness of any personal protection method is dependent on compliance. Data generated from the comparison of the intention-to-treat and per-protocol analyses [51–53] will give useful information about compliance among the troops.

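### Read as worded, the per-protocol antimalarial exclusion looks back over the interval that prompted treatment, so it selects person-time on the outcome and would drop clinic-detected infections from that analysis

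*Protocol article*

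**What the plan says.** The section on statistical methods for primary and secondary outcomes {20a} makes intention-to-treat the primary analysis and then adds: "A per-protocol analysis will also be performed where person-time at risk will be adjusted to exclude 2 weeks of follow-up of participants who" meet one of three criteria. The first is non-compliance with the lotion. The others read "2) have taken antimalarials or (3) have travelled outside the camp for personal reasons within the previous 2 weeks".

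Four other places bear on the second criterion:

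- **Concomitant care {11d}:** "All antimalarials will be dispensed to only participants with positive RDT". Just before this: "Participants are advised to refrain from self-prescription of any medication".
- **Primary outcome {12}:** infection is found by qPCR at the two-weekly surveys "and by passive case detection at the camp clinic in the case of illness". The same paragraph takes a 14-day window following any malaria treatment out of time at risk.
- **Collection of outcomes {18a}:** "Treatment will be offered to all malaria-infected participants, and all treatment details will be filled in and added to the patient file".
- **Discussion:** "Data generated from the comparison of the intention-to-treat and per-protocol analyses" is expected to inform on compliance among the troops.

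**The concern.** A per-protocol exclusion should remove time in which the participant departed from the assigned intervention. Lotion non-compliance fits that purpose. Antimalarials dispensed by the trial do not, because they are given as a consequence of infection.

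Take a recruit who falls ill on day 5 of an interval, is RDT-positive at the clinic and is treated. At the day-14 survey this recruit has taken antimalarials in the preceding 2 weeks. If those 2 weeks are removed, the endpoint event goes with them, so person-time is selected on the outcome.

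The per-protocol analysis would then move towards survey-detected infection only. The Discussion would read the gap between it and the intention-to-treat result as a compliance effect, when part of the gap would be deleted cases.

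**Working it through.** **1. Which reading does the text support?**

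- *Look-back.* The three criteria share one list and one 2-week removal. Lotion compliance is judged per 2-week interval (Defining compliance). The travel rule under adherence {11c} removes the 2 weeks before testing. Applied in the same way, the antimalarial criterion removes the interval in which treatment was given.
- *Forward.* The 14 days after treatment are removed. The Primary outcome section already does this, so the criterion would add nothing.
- *Mixed.* The interval is removed but the event is kept. This leaves an event with no time at risk, which a rate model cannot use sensibly.

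**2. Inputs.** From Sample size {14}: rates of 0.41 (PTU + DEET) and 0.27 (ETU + DEET) per person-year, an IRR of 0.66, 12 clusters of 40 for 12 months per arm (480 person-years), 89% power and a CI of 0.49 to 0.88. Two inputs are not given and are assumed: the clinic-detected share *s*, and the between-cluster CV *k*. A two-sided 5% level is also assumed.

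**3. The plan's own figure.** Expected events are 0.41 × 480 = 196.8 and 0.27 × 480 = 129.6. With SE² = 1/196.8 + 1/129.6 + 2k²/12 and power = Φ(|ln IRR|/SE − 1.96):

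- 89% power is reached at k of about 0.16. k = 0 gives 96% and k = 0.30 gives 71%.
- The stated CI implies SE = ln(0.88/0.49)/3.92 = 0.149, hence k of about 0.24 and power of about 79%.

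The power figure therefore cannot be confirmed without k. The range 0.16 to 0.24 is used below.

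**4. Look-back reading, equal share in both arms.** Events left are 196.8(1 − s) and 129.6(1 − s). Person-time lost in an arm is events × s × 14/365, at most 4.5 of 480 years (0.9%) at s = 60%. The Poisson part of the variance, 0.012797, is divided by (1 − s). The cluster part stays at 0.004267 (k = 0.16) or 0.009600 (k = 0.24).

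| Assumed share | Events left, PTU + DEET / ETU + DEET | SE rise, k = 0.16 | SE rise, k = 0.24 | SE rise, no clustering |
|---|---|---|---|---|
| 20% | 157 / 104 | 9.0% | 6.9% | 12% |
| 40% | 118 / 78 | 22.5% | 17.5% | 29% |
| 60% | 79 / 52 | 45.8% | 36.3% | 58% |

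For example, at s = 40% and k = 0.16: √[(0.012797/0.6 + 0.004267)/(0.012797 + 0.004267)] = 0.1600/0.1306 = 1.225.

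The protocol's efficacy and compliance inputs in fact give 0.68 × (1 − 0.7 × 0.8) = 0.299 for ETU + DEET, not 0.27. That is a separate matter. Using 0.408 and 0.299 changes the SE rises only to 6.7–8.8%, 17.1–22.2% and 35.5–45.2%. The IRR hardly moves when shares are equal.

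**5. Look-back reading, unequal shares.** The per-protocol IRR is about 0.66 × (1 − s in ETU + DEET)/(1 − s in PTU + DEET). With 50% in PTU + DEET:

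- 40% in ETU + DEET: 0.66 × 0.6/0.5 = 0.79
- 60% in ETU + DEET: 0.66 × 0.4/0.5 = 0.53

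**6. Forward reading.** All 197 and 130 events stay. Person-time falls by at most 196.8 × 14/365 = 7.5 of 480 years (1.6%), and the IRR is 0.655 to 0.658.

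**The case against.** The strongest reply is that the analysis section speaks only of adjusting person-time. It does not say that infections are dropped, or that the removed weeks precede treatment. Treatment and travel are paired, with the same length, in the forward windows of the Primary outcome section, so the criterion may be a loose restatement of those. A clinic diagnosis on day 5 is also its own detection point, and at that moment no antimalarial had yet been taken. This stands in part: a reader might infer that the plan definitely deletes every clinic-detected infection, and the text does not establish that. But the charitable reading makes the criterion redundant, and the wording looks back.

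A reader might also infer that the problem exists however the endpoint is defined. It does not. The Abstract's Method and the section on estimates of protective efficacy can be read as counting qPCR-detected infections only. If a clinic RDT case is not an endpoint event, none is deleted. The problem depends on the Primary outcome section, which includes "by passive case detection at the camp clinic in the case of illness".

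Nor is every antimalarial course a marker of the outcome. Self-prescription is discouraged but not ruled out, and excluding such time is legitimate. The section on collection of outcomes offers treatment to all infected participants, a wider group than the RDT-positive group under concomitant care. Treatment still follows infection either way, but the two statements conflict.

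Finally, the trial is double-blind and nothing in the protocol indicates that clinic shares differ between arms. Operational detail of this kind is often left to an analysis plan. However, the protocol does state a rule here, and an analyst following its words would most naturally remove the wrong interval.

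**Conclusion.** The concern holds for the rule as worded. On its look-back reading the antimalarial criterion conditions on the outcome and would drop clinic-detected infections, as the Primary outcome section defines them, from the per-protocol analysis. On the forward reading it does no harm and adds nothing.

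The reach is limited to the per-protocol analysis and to its comparison with intention-to-treat. The primary analysis is unaffected. Survey-detected infections stay unless they are treated within the same interval.

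The size rests on assumed clinic shares. With equal shares the cost is precision, and the increase in the SE once clustering is allowed for is the relevant one; the 12%, 29% and 58% without clustering overstate it. Bias in the IRR needs unequal shares. The values 0.79 and 0.53 show what such a difference would do and are not predictions.

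**What to change.** Reword the antimalarial criterion in the statistical methods section {20a}:

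- Count the infection that prompted treatment, and the person-time up to the treatment date.
- Exclude only the 14 days after treatment, consistent with the Primary outcome section.
- Keep an antimalarial exclusion as a deviation only for antimalarials taken outside the trial, from the date taken onward.

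Two sets of statements must also be reconciled: who receives treatment (concomitant care {11d} against collection of outcomes {18a}), and whether clinic-detected cases are endpoint events (the Abstract's Method, Primary outcome, and estimates of protective efficacy).

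The change to the analysis rule takes a sentence or two and no new data collection, since treatment details already go into the patient file. The Trial status section says that recruitment has not begun, so it can be made before any outcome data exist.
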